### Relevant concomitant care permitted or prohibited during the trial {11d}

There are no relevant restrictions on concomitant care or interventions during this study. All standard concomitant care is permitted.

### Provisions for post-trial care {30}

The sponsor maintains liability insurance in accordance with article 7 of the Medical Research Involving Human Subjects Act (WMO). Aftertreatment following the PWB protocol is already implemented in several hospitals in the Netherlands, including for DIACFs. While no adverse effects have been noted from clinical experience, there may be potential risks that are currently unknown. Additionally, a recent retrospective study, not yet published, and a systematic review and meta-analysis reported no negative effects on patients’ reported quality of life, pain, or complication rates.

### Outcomes {12}

#### Primary outcome

The primary outcome is the functional outcome score, defined by the American Orthopaedic Foot & Ankle Society (AOFAS). The AOFAS score is a clinician-based assessment tool that integrates both subjective and objective information. Patients provide self-reports on their pain levels, while physicians evaluate alignment. This scoring system is intended to assist physicians in standardizing patient assessments, thereby facilitating the comparison of study results with previous data. Scores on the AOFAS scale range from 0 to 100, with a score of 100 points indicating optimal health for the foot and ankle [21]. Time points: measured at 2 weeks, 6 weeks, 12 weeks, and 6 months post-surgery.

#### Secondary outcomes

Secondary outcomes encompass several measures.The Maryland Foot Score (MFS): The MFS is a tool for assessing foot disorders, comprising evaluations of pain, gait, functional activities, and cosmesis. Scores range from 0 to 100 points, with < 50 indicating poor, 50–74 as fair, 75–89 as good, and 90–100 as excellent outcomes [22]. Time points: collected at 2 weeks, 6 weeks, 12 weeks, and 6 months post-surgery.Health-related quality of life (HRQoL) using the EuroQoL 5-Dimension 5-Level (EQ-5D-5L): This self-administered questionnaire comprises five dimensions (mobility, self-care, daily activities, pain/discomfort, and depression/anxiety), each rated on five levels. Utilities calculated using preferences from the Dutch tariff will enable Quality Adjusted Life Years (QALY) scoring, besides the questionnaire is recommended by the Dutch guidelines [23, 24]. Time points: collected at baseline, 2 weeks, 6 weeks, 12 weeks, and 6 months post-surgery.Radiographical characteristics: Evaluation of Böhlers angle and posterior facet joint alignment via radiographic assessment by a blinded radiologist will be conducted at scheduled physician visits. CT scans early post-operatively and at 6 months will be used to measure differences in Böhlers angle and posterior joint alignment [25]. Differences in the Böhlers angle and posterior joint alignment (Δ = CT_6months_—CT_post-op._) will be calculated. Normal Böhlers angle ranges between 25° and 40° [26]. Intra-articular step-off or gap < 2 mm of the posterior facet is considered well-reduced [3]. Time points: early post-operative (‘baseline’) and at 6 months post-surgery CT scan.Medical consumption and productivity: Measured using the Medical Consumption Questionnaire (iMCQ) and Productivity Costs Questionnaire (iPCQ). The iMCQ assess healthcare utilization, while the iPCQ captures productivity losses. The iPCQ and iMCQ are generic and complimentary questionnaires, that can be used in every indication and are adapted to the context of this study [27]. Time points: collected at baseline, 12 weeks, and 6 months post-surgery.Total complication rate: A wound infection is defined as (but not limited to) purulent wound drainage, inflammation, erythema, fever, increased white blood cell count, increased C-reactive protein and/or increased erythrocyte sedimentation rate, necessitating admission for antibiotic treatment and/or revision surgery for infection.A dislocation is defined as the migration of fracture parts, defined as >3 mm articular step-off or gap and/or varus/valgus malalignment > 5° after weight bearing. A non-union is defined as no radiographic union achieved after 6 months or no progress in healing. Failure of osteosynthesis is defined as loosening or breakage of implants, including the rate of reoperation (e.g., leading to removal of material, arthrodesis). Postoperative arthritis will be screened on CT scans. Time points: evaluated at 2 weeks, 6 weeks, 12 weeks, and 6 months post-surgery.

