### Intervention description {11a}

#### Permissive weight bearing

The PWB protocol represents a relatively new approach to early weight bearing, enabling earlier postoperative weight bearing. Progression of weight bearing is determined by the patient’s subjective experience, such as pain levels and weight bearing tolerance, along with the clinical expertise of the treating physician and physiotherapist, in line with the PROMETHEUS protocol [12]. The rehabilitation regimen commences with 2 weeks of immobilization to facilitate wound healing. Subsequently, patients are allowed to bear as much weight as tolerated, guided by their pain levels and comfort [12].

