#### Restrictive weight bearing

The RWB protocol adheres of 8 to 12 weeks of postoperative weight bearing restriction, in the range of 0–10%, so-called *touching load*, as outlined in the current AO Guidelines [16]. Following this initial phase, which entails restricted weight bearing, a gradual increase in weight bearing is implemented. This entails a weekly increment of 25% over the course of 4 weeks. During each patient-physician encounter, the weight bearing advice provided to the patient is meticulously recorded. This includes whether the recommendation is for unloaded, partial weight bearing with clarification, or full weight bearing. Furthermore, any additional advice imparted to the patient is also documented.

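### The dislocation component is meant to capture migration, but it is fixed as an absolute threshold with no baseline and tied to weight bearing, which starts at different times in the two arms

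*Protocol article*

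**What the plan says.** Within the total complication rate (Protocol article, Secondary outcomes), the definition reads "A dislocation is defined as the migration of fracture parts, defined as >3 mm articular step-off or gap and/or varus/valgus malalignment", and its last limb is "varus/valgus malalignment > 5° after weight bearing". No baseline image is named. Complications are assessed on the same schedule in both arms: "Time points: evaluated at 2 weeks, 6 weeks, 12 weeks, and 6 months post-surgery".

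The start of loading differs by design (Intervention description {11a}). For PWB, "The rehabilitation regimen commences with 2 weeks of immobilization to facilitate wound healing", after which loading is as tolerated. For RWB, "The RWB protocol adheres of 8 to 12 weeks of postoperative weight bearing restriction", limited to a touch load of 0–10%, followed by a build-up: "This entails a weekly increment of 25% over the course of 4 weeks".

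Three other provisions matter:
- A separate radiographic outcome takes the 6-month CT minus the early post-operative CT for Böhler's angle and posterior joint alignment, read by a blinded radiologist. It is not linked to the dislocation definition.
- The eligibility criteria admit Sanders II–IV fractures and set no limit on the quality of reduction achieved.
- The statistical methods section compares any complication between arms by logistic regression.

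**The concern.** There are two separate weaknesses.

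**State or movement.** A step-off above 3 mm describes how the joint looks, not whether it moved. A joint left at, say, 3.5 mm by surgery meets the number without any migration. Such cases should occur about equally in both arms, so they add the same background to each and pull a real difference towards none. In a trial meant to show that early loading is not worse, that error reassures.

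**Timing tied to the randomised exposure.** If displacement counts only once weight bearing has begun, a displacement seen at the 6-week visit is eligible in PWB but not yet in RWB. The article says that the allocated aftertreatment cannot be blinded and has the local investigator screen for complications. A clause that depends on loading status therefore invites the classifier to use the allocation.

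The component matters because displacement under load is the specific harm that the article's introduction raises, and the introduction calls the safety of early weight bearing after surgery uncertain.

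**Working it through.** **The plan's own figure.** The only computed figure is the sample size. With margin 5, SD 8.5, true difference 0, one-sided 2.5% and 80% power: n = 2 × (1.960 + 0.842)² × 8.5² / 5² = 45.4, so 46 per arm and 92 in total; 92 / 0.80 = 115. This reproduces, and nothing below changes it. The article gives no expected rate of dislocation or complications, so every rate below is an assumption.

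**Length of the countable window, strict reading.** Window = 26 weeks minus the start of weight bearing.
- PWB: 26 − 2 = 24 weeks.
- RWB, start after week 8: 26 − 8 = 18 weeks; ratio 24/18 = 1.33.
- RWB, start after week 12: 26 − 12 = 14 weeks; ratio 24/14 = 1.71.

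The start differs by 8 − 2 = 6 to 12 − 2 = 10 weeks. The eligibility section speaks of 8 to 10 weeks without weight bearing, which lies inside this range.

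**What that could do at most.** Assume equal true 6-month risk R in both arms and a constant hazard λ = −ln(1 − R)/26. The counted risk over w weeks is 1 − exp(−λw).

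| Assumed R | PWB (24 wk) | RWB (18 wk) | RWB (14 wk) | Ratio PWB/RWB |
|---|---|---|---|---|
| 5% | 4.62% | 3.49% | 2.72% | 1.33 to 1.70 |
| 10% | 9.27% | 7.03% | 5.52% | 1.32 to 1.68 |
| 15% | 13.93% | 10.64% | 8.38% | 1.31 to 1.66 |

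These ratios arise with no true difference, but only if every RWB displacement before loading is lost for good. A step-off that persists is still visible on the 6-month CT, so they are upper bounds.

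**Dilution by residual step-off.** Let q be the share of each arm above the threshold after surgery and p the true migration risk. The counted risk is q + (1 − q)p.
- Assumed q = 10%, p = 5% against 10%: 0.10 + 0.90 × 0.05 = 14.5% and 0.10 + 0.90 × 0.10 = 19.0%. The ratio falls from 2.0 to 1.31; the difference falls only from 5.0 to 4.5 points.
- Assumed p = 15% in PWB against 5% in RWB, 46 per arm, two-sided 5% comparison of two proportions:

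| q | Counted PWB | Counted RWB | Ratio | Power |
|---|---|---|---|---|
| 0 | 15.0% | 5.0% | 3.00 | 36% |
| 5% | 19.3% | 9.8% | 1.97 | 25% |
| 10% | 23.5% | 14.5% | 1.62 | 19% |
| 20% | 32.0% | 24.0% | 1.33 | 13% |

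With equal true risks of 10%, the counted ratio stays at 1.0 for every q: this error dilutes but does not create a difference.

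**After the fix.** With change from the post-operative CT, q drops out. With one calendar window, equal true risk gives a ratio of 1.0.

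**The case against.** The best defence is that the wording, read sensibly, does less harm than the arithmetic suggests.

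- **The timing phrase may qualify only malalignment**, and a 0–10% touch load might itself be called weight bearing. Both readings are possible, so it cannot be asserted that the definition counts only events after loading. But a definition that allows several readings lets the same patient be classified differently.
- **Migration implies movement**, and a CT before first mobilisation exists to judge it. A reader might infer that unreduced fractures are counted as migration by rule. The article does not say so; this is a risk of applying the number literally. The text does, however, define migration by that number.
- **Most early displacement in RWB would still be caught.** Assessment times are identical, both arms are loading well before the 6-month CT, and implant failure and reoperation are counted with no weight-bearing clause. This stands. What can be lost is narrow: early displacement that neither persists nor leads to another counted event.
- **The two effects do not both apply at full strength.** A pure status read at 6 months largely removes the window problem, and a strict requirement of movement after loading removes the residual step-off. This also stands.
- **Change is already measured, blinded, in the radiographic outcome.** This mitigates for the joint surface. The complication count does not draw on it, and varus/valgus is not part of it.

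**Conclusion.** The concern holds in limited form. The definition names migration, measures a state without a baseline, and on its natural reading is timed from a moment that comes 6 to 10 weeks later in RWB. Literal use can dilute a real difference through residual step-off and can miss a narrow class of early RWB events, which would count against PWB.

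The size cannot be estimated from the documents. The window ratio of 1.3 to 1.7 rests on the strict reading and is a ceiling; the dilution figures rest on assumed rates. A reader might infer that the complication comparison is biased against PWB by that ratio, or that it can no longer be read as a treatment effect. Neither is supported: persistent displacement is seen at 6 months in both arms, and randomisation balances residual step-off in expectation. Nor does the article call this its main safety comparison. What may be distorted is one component of a secondary outcome; the primary analysis and the sample size are untouched. The change is still worth making, because it replaces a stated rule with a better one at little cost.

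**What to change.** In Outcomes {12} and the case report form:

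1. Define dislocation as worsening from the early post-operative CT by an amount in mm or degrees that the clinical team sets.
2. Use the same calendar window in both arms, from the post-operative CT to 6 months, and remove the reference to weight bearing.
3. Base the main comparison on the 6-month CT read by the blinded radiologist.
4. Count displacement that led to earlier revision as an event.
5. Report separately the events found only on interim X-rays. These are taken as indicated, by staff who cannot be blinded to the regime, so detection may differ by arm.

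The cost is small. Both CTs are planned and the number of patients does not change. The article's list of CT readings does not mention varus/valgus, so that reading should be confirmed or added. The downside is less direct comparison with literature that uses an absolute threshold.

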
### Participant timeline {13}

Regular follow-up will be performed for both weight bearing regimes. Appointments will be scheduled at 0, 2, 6, and 12 weeks, and at 6 months (Fig. 2).

**Fig. 2 Fig2:**

Overview of the measurements

### Sample size {14}

To our knowledge, there is no literature available that directly compared our primary outcome (AOFAS Score) in PWB versus RWB for surgically treated patients with DIACFs. Therefore, unfortunately, the MCID is unknown for the AOFAS Score [28, 29].

However, the estimated minimal clinical difference (MCID) can be calculated as one half of the standard deviation (0.5 SD) [30]. Preliminary results of a systematic review that is currently performed by our group, found a mean AOFAS Score of 83.7 (SD 8.5) for the RWB group. 0.5 × 8.5 results in a MCID of 4.3, respectively.

Besides, a recent Cochrane review reported a MCID for the AOFAS Score in other foot conditions that range from 2.0 to 7.9 [29]. This results in a mean MCID of (2.0 + 7.9)/2 = 5, respectively.

For this sample size calculation, a MCID of 5 points was assumed, approximating a 0.5 SD of the estimated mean AOFAS score after RWB for surgically treated patients with DIACFs [30].

In order to be able to detect such a difference between the two groups, assuming that an equal number of patients in both groups will be included, with an alpha of 5% and beta of 20% (power 80%), a pooled SD of 8.5 and a true difference of zero points between the RWB and PWB group the sample size should be at least 46 for both groups = 92 in total. Anticipating a 20% drop out a total of 115 patients must be recruited for this study. The sample size calculation was performed with a two-sample mean test for non-inferiority using the TrialSize package within “R.”

### Recruitment {15}

Each medical institution participating in “the PIONEER study” will appoint a Local Investigator (LI). The Coordinating Investigator (CI) will oversee the trial and provide guidance to all LIs across each medical institution. Together, the LIs (comprising trauma or orthopedic surgeons) and the CI will constitute “the PIONEER study” group. The LIs will actively screen patients for eligibility at their institution’s emergency department or outpatient clinic. In cases where there is uncertainty regarding the eligibility criteria, the LI will communicate with the CI, who will make the final decision.

## Assignment of interventions: allocation

### Sequence generation {16a}, concealment mechanism {16b} and implementation {16c}

After recording patient characteristics from the electronic medical records, patients will be randomly assigned to one of the two aftertreatment protocols in a 1:1 ratio. Randomization will be conducted using a web-based computer system (Castor EDC) developed by MEMIC (the center for data and information management at the Faculty of Health, Medicine, and Life Sciences of Maastricht University and MUMC +). Block randomization with random permuted block sizes will be employed. If a replacement patient is needed, they will be re-randomized following the same conditions.

## Assignment of interventions: blinding

### Who will be blinded {17a}

Blinding for the type of aftertreatment will not be possible. However, in Castor EDC, randomization rights will be set up correctly to ensure that all users who need to be blinded do not have access to the allocation data. Only users with the “view randomization” right, will be able to see to which group a participant (record) has been allocated; so-called *concealed allocation*.

### Procedure for unblinding if needed {17b}

This is not applicable as blinding is not feasible for this study. Consequently, there is no need for an unblinding procedure.

## Data collection and management

### Plans for assessment and collection of outcomes {18a}

Baseline characteristics will be retrieved by the LI from the electronic patient file. A clinical assessment will be conducted by the LI and recorded in the case report form using the online data management system Castor. Subsequent follow-ups will involve screening the electronic patient file to evaluate any late complications, re-interventions, re-admissions, duration of medical institution stay, and consultations at the medical institution. The LI of the medical institution or, if necessary, the CI will carry out this screening and follow-up assessment. All data collected will also be documented in the case report form by either the LI or CI. In the event of any queries regarding the data, the CI will be contacted by the LI or site investigator.

Additionally, the patients will be administered questionnaires at 0, 2, 6, and 12 weeks, as well as 6 months post-surgery, irrespective of the rehabilitation protocol.

### Plans to promote participant retention and complete follow-up {18b}

To promote participant retention and ensure complete follow-up, LIs and CIs will call patients who do not complete their questionnaires. This approach aims to maximize data collection and maintain the integrity of the study outcomes.

### Data management {19} and confidentiality {27}

All questionnaires will be distributed and completed digitally. Enrolled patients will receive a link via email or SMS, facilitated by Castor, an electronic data capture and management application [31]. Castor is a validated system and approved by external auditors and complies with relevant laws and regulations, including ICH E6 Good Clinical Practice, 21 CFR Part 11, European Union Annex 11, General Data Protection Regulation, HIPAA (US), ISO 9001 and ISO 27001 [31].

In addition to standard care, preoperative and postoperative (prior to initial mobilization) a CT scan of the injured calcaneus will be conducted. An additional CT scan will be performed at 6 months postoperative. Subsequent radiographic follow-up will involve X-rays as indicated, also in accordance with standard care. Interpretation of CT scans and X-rays will encompass evaluation of Böhlers angle alignment, posterior facet joint alignment (including step-off and gap assessment), and identification of posttraumatic arthritis.

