## Discussion

The current paper outlines the protocol for a multicenter randomized controlled trial to be conducted in 11 hospitals across the Netherlands. It provides comprehensive details on the study’s objectives, methodology, including patient flow, randomization procedures, recruitment strategies, rehabilitation protocols, and data analysis methods. Additionally, it offers guidance for presenting and publishing the results. Notably, this study will be the first to establish an optimal rehabilitation regimen for patients with DIACFs, and it possesses several strengths. Firstly, it adopts a randomized controlled trial design, widely regarded as the gold standard in clinical research. The involvement of multiple Dutch hospitals enhances the generalizability of the findings. Moreover, this design minimizes potential biases inherent in observational studies, facilitating a more accurate assessment of intervention effectiveness.

However, several limitations should be acknowledged. Firstly, the inevitable heterogeneity in surgical treatment across participating centers may impact protocol consistency and consequently, outcomes. Standardized protocols and staff training will address this concern. Secondly, compliance bias may arise as patients may not strictly adhere to allocated weight bearing regimes. Again, standardized protocols and staff training will mitigate this bias. Thirdly, patient blinding is unfeasible for rehabilitation, potentially compromising methodological rigor and introducing bias into results. However, blinding will be implemented for radiological evaluations. Additionally, the 1-year follow-up period limits assessment of longer-term outcomes, although the greatest effect of early weight bearing is typically observed within the first 3 to 6 months post-surgery.

In conclusion, existing retrospective literature provides inadequate methodological data to determine the superiority of one rehabilitation protocol over another. The PIONEER study will offer evidence on whether to favor one weight bearing protocol over another and will ascertain the safety and efficacy of these protocols for patients with DIACFs.

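### Three imaging features that define complications are not named in the blinded read, and the plan is inconsistent on when X-rays are taken and how far imaging is blinded

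*Protocol article*

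**What the plan says.** **The blinded read.** The Secondary outcomes section (radiographical characteristics) states: "Evaluation of Böhlers angle and posterior facet joint alignment via radiographic assessment by a blinded radiologist will be conducted at scheduled physician visits". It then gives its own time points, an early post-operative CT and a 6-month CT, and defines the outcome as the change between them.

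**What is read, and when X-rays are taken.** Data management {19} and confidentiality {27} states: "Interpretation of CT scans and X-rays will encompass evaluation of Böhlers angle alignment, posterior facet joint alignment". The list goes on to step-off and gap, and to posttraumatic arthritis. The same section plans the post-operative and 6-month CTs without condition and then adds: "Subsequent radiographic follow-up will involve X-rays as indicated, also in accordance with standard care".

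**What counts as a complication.** Under total complication rate, the Secondary outcomes section defines dislocation by step-off or gap above 3 mm and/or varus/valgus malalignment above 5°. Non-union is absence of radiographic union after 6 months, or no progress in healing. Failure of osteosynthesis is loosened or broken implants, with reoperation included. Complications are evaluated at 2, 6 and 12 weeks and at 6 months.

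**Who records them.** Plans for assessment and collection of outcomes {18a} has the patient file screened for late complications and re-interventions: "The LI of the medical institution or, if necessary, the CI will carry out this screening and follow-up assessment". Who will be blinded {17a} says that the aftertreatment itself cannot be blinded.

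**The general claim.** The Discussion says that "blinding will be implemented for radiological evaluations", with no limit on items.

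**The analysis.** Secondary study parameters compares the occurrence of any complication between arms by logistic regression.

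**The concern.** The introduction names fixation failure and fragment migration, leading to malunion or non-union, as the harms of excessive loading. It also says that the safety of early weight bearing after this surgery is still uncertain. Implant failure, union and varus/valgus alignment are therefore among the findings most relevant to the risk of the permissive arm, yet they are the ones not named for the blinded reader.

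Where an X-ray is taken only when someone sees a reason, that person usually knows the arm. A clinician uneasy about early loading may image permissive-arm patients more readily and label more findings; one who favours it may do the opposite. Two definitions leave room for judgement: lack of progress in healing, and reoperation. The arm comparison of complications could then partly reflect how often patients were imaged and who judged the images.

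**Working it through.** The plan gives no complication rate, detection rate or X-ray frequency, so there is no figure on this point to reproduce. The sample size (46 per group, 92 in total, 92 / 0.80 = 115) concerns the AOFAS score and is not touched.

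**Step 1. Match each imaging-defined complication to the reading items.**

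| Feature (Secondary outcomes) | Named in the blinded read (Secondary outcomes) | Named in the interpretation list (Data management {19}) |
|---|---|---|
| Step-off or gap > 3 mm (dislocation) | Yes, as posterior facet alignment | Yes |
| Varus/valgus > 5° (dislocation) | No | No |
| Radiographic union (non-union) | No | No |
| Implant loosening or breakage (failure of osteosynthesis) | No | No |
| Arthritis | Not named, but screened on CT | Yes |

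Three features appear in a definition and in neither reading description. The Discussion's general statement could cover them, so the three places do not agree on the scope of the blinded read.

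**Step 2. Compare the imaging schedules.** One section ties radiographic assessment to scheduled visits; the other makes X-rays discretionary. Both cannot govern X-rays at the 6- and 12-week visits. The CT-based outcome is safe, because its two time points are fixed and the extra CT applies to both groups (abstract, Methods). Exposure to discretionary imaging is therefore confined to events found before the 6-month CT. That the X-ray sentence refers to this interval is the likely reading, but it is not stated.

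**Step 3. Follow the record.** File screening by the local or coordinating investigator supplies late complications to the logistic regression. No blinding of these investigators and no blinded adjudication is described.

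**Step 4. Illustrate the possible distortion, on assumed inputs only.** Let the true rate p be the same in both arms, with detection a in one arm and b in the other. The apparent odds ratio is [pa/(1 − pa)] / [pb/(1 − pb)].

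| p | a = b = 90% | 90% vs 60% | 100% vs 50% |
|---|---|---|---|
| 5% | 1.0 | 4.5% vs 3.0%, OR 1.52 | 5.0% vs 2.5%, OR 2.05 |
| 10% | 1.0 | 9% vs 6%, OR 1.55 | 10% vs 5%, OR 2.11 |
| 20% | 1.0 | 18% vs 12%, OR 1.61 | 20% vs 10%, OR 2.25 |

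For p = 10% and 90% vs 60%: (0.09/0.91) / (0.06/0.94) = 1.55. If the better-detected arm is the other one, the ratio inverts (1/1.55 = 0.65). The table treats all detection as discretionary. An event that persists to the 6-month CT and is read equally in both arms moves toward the 1.0 column.

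**The case against.** The strongest reply is that this rests on silence. The Discussion extends blinding to radiological evaluation without restriction, and the interpretation list says what reading will cover without saying that it covers nothing else. The article condenses a longer protocol, and an item-by-item reading form belongs there. This stands in part. A reader might infer that implant failure, union and varus/valgus are excluded from blinded reading; the documents do not say so, only that these items are not named where the read is described. The absence of a form is no finding. What remains is that the article itself states the reader, the reading list and the complication definitions, and these do not match.

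A reader might also infer that unblinded staff decide who is imaged and who counts as a mechanical complication. That goes too far. A 6-month CT is planned in both arms, it falls at the time by which non-union is mainly defined, and persisting hardware failure or malalignment could be read on it. Step-off/gap dislocation is already within the blinded read, and arthritis is on the reading list.

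The conflict over schedule is also milder than it first looks, because the radiographic change outcome has fixed CT time points of its own. What is left is the scheduled-visit wording against discretionary X-rays, which matters for complications counted at 2, 6 and 12 weeks.

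Finally, the detection rates in the illustration have no source in the documents. That is correct, and no size should be claimed from them.

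**Conclusion.** The point holds in limited form. Three imaging features that define complications are not named in the blinded read or the interpretation list, the sections differ on the X-ray schedule and on the scope of blinding, and late complications are recorded by investigators for whom no blinding is described. Mechanical complications found before the 6-month CT are therefore open to unequal detection and classification by arm.

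The direction is unknown, and the size cannot be derived from the documents. Under the assumed detection gaps the odds ratio with no true difference runs from 1.52 to 2.25 or the inverse; with equal detection it is 1.0. Events still visible on the 6-month CT would pull it toward 1.0 if read equally in both arms. The issue concerns components of one secondary safety outcome. Confidence is moderate, because the full protocol may settle the scope of the read.

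**What to change.** 1. Reconcile Secondary outcomes, Data management {19} and the Discussion on whether interim X-rays are scheduled or discretionary, and on what the blinded read covers.
2. Add implant loosening or breakage, union status and varus/valgus angle to the form that the planned blinded radiologist completes on the post-operative and 6-month CTs.
3. Have the same radiologist read, blinded, any discretionary X-ray that led to a mechanical complication call or a reoperation.
4. Keep every complication at 2, 6 and 12 weeks and 6 months in the planned any-complication comparison. A CT-only count should not replace it, since it could drop real early safety events.
5. Add a between-arm comparison of the imaging-defined components from the blinded CT read, among patients with a 6-month CT, and report the number of interim X-rays by arm.

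The cost is a slightly longer read, re-reading of a limited set of X-rays and one additional analysis. No new scan or reader is needed. The added comparison loses patients without a 6-month CT: if the plan's 20% dropout applied to it, 115 × 0.80 = 92 would remain. Blinded re-reading of discretionary X-rays corrects classification but not the decision to image, which is why the X-ray counts by arm are needed beside it.
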